**Fig. 3 Fig3:**
[figure not shown]
Location of acupoints. BL2, Cuanzhu, on the medial end of the eyebrow; GB14, Yangbai, directly above the pupil, 1 cun above the midpoint of the eyebrow; Shangming, in the orbital cavity and at the midpoint of the orbital margin; SJ23, Sizhukong, in the depression at the lateral end of the eyebrow; LI14, Bi’nao, at the stop of deltoid muscle on the line between LI15 (Jianyu) and Quchi (LI11), 7 cun above Quchi (LI11); Sham LI14, 1 cm backward to Bi’nao; SJ5, Waiguan, on the line joining Yangchi (SJ4) and the tip of elbow, 2 cun above the dorsocarpal transverse crease between the ulna and radius; KI6, Zhaohai, in the depression directly below the tip of the medial malleolus

**Table 2 Tab2:** Acu-points and needle insertion procedure

Acupuncture point	Direction	Depth (mm)
BL2 (Cuanzhu, affected side)	Transversely, along with geisoma	5–10
GB14 (Yangbai, affected side)	Transversely, toward geisoma	5–10
SJ23 (Sizhukong, affected side)	Obliquely toward partes temporalis	5–10
Shangming (affected side)	Transversely, along with gap between the eye socket and the eyeball	5–10
LI14 (Bi’nao, affected side)	Perpendicular to the skin	20–30
SJ5 (Waiguan, bilateral)	Perpendicular to the skin	10–20
KI6 (Zhaohai, bilateral)	Perpendicular to the skin	5–10

#### Allowed or prohibited concomitant treatment

The use of medications or other therapies for hypophasis will be discouraged during this trial. The treatments of individuals for other underlying chronic diseases will be allowed if they do not change during the study period and will be recorded accordingly, including the name, dosage, and duration of the medication. If a violation occurs during the study period, the patient will be excluded from the study.

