#### Quality control

All acupuncturists and assessors will be required to undergo specialized training before the trial in order to guarantee consistent practices. The training program will include diagnosis, inclusion and exclusion criteria, the location of the acu-points, acupuncture manipulation techniques, and completion of the case report forms. Dropouts and withdrawals from the study will be recorded based on the intervention and follow-up periods. This trial will be monitored by the Scientific Research Department of Baoshan Hospital of Integrated Traditional Chinese Medicine and Western Medicine, Shanghai. A qualified clinical research investigator will be specified by the department office and periodic monitoring will guarantee accuracy and quality throughout the study.

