### Withdrawal and dropout

All participants will have the right to withdraw from this study at any time. Participation will be terminated at any stage if the individual refuses to continue, withdraws consent, or violates the inclusion or exclusion criteria. The investigator may also exclude the participants from the study in order to protect their safety and/or if they are unwilling or unable to comply with the required study procedures after consultation with the institutional review board (IRB).

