### Statistical methods

#### Sample size calculation

The enumeration data of parallel-controlled trial (1:1:1) are analyzed statistically using two-sided superiority test, where α = 0.05, power = 90%. The formula used for the calculation was as follows:$$ n\kern0.5em =\kern0.5em \frac{{\left({Z}_{1-a}+{Z}_{1-\upbeta}\right)}^2\kern0.5em \times \left({\sigma}_1^2+{\sigma}_2^2\right)}{\delta^2} $$

The change in the standard deviation of ECWM score before and after the treatment in the control group was presumed as 1 point and that in the treatment group as 3 points. This will be considered clinically significant if the change in the ECWM score before and after the treatment in the treatment group is 2 points higher than that in the control group, and the sample size was estimated as follows:$$ n\kern0.5em =\kern0.5em \frac{{\left({Z}_{1-a}+{Z}_{1-\upbeta}\right)}^2\kern0.5em \times \left({\sigma}_1^2+{\sigma}_2^2\right)}{\delta^2}\kern0.5em =\kern0.5em \frac{{\left(1.96+1.28\right)}^2\kern0.5em \times \left({1}^2+{3}^2\right)}{2^2}\kern0.5em =\kern0.5em 26 $$

Thus, a minimum of 27 patients was estimated in each group. The dropout rate is considered to be 20%; therefore, at least 33 patients should be enrolled in each group. Hence, a total of 99 patients are required to conduct this study.

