#### Statistical analysis

In this study, rather than the investigator, professionals will analyze the data using intention-to-treat and per-protocol approaches. The demographic and clinical characteristics of the participants (such as sex and age) will be processed based on descriptive analyses. The ECWM values and ESA scores will be compared as a baseline measurement. The quantitative data will be presented as average, standard deviation, median value, and range, while the qualitative data will be presented as the frequency and percentage.

For the primary and secondary outcome measurements, one-way ANOVA test will be applied to identify the differences between the of ECWM values and ESA scores among the groups. In case of abnormally distributed data, Kruskal–Wallis H test will be performed.

All AEs reported during the study will be included in the clinical report; then, the prevalence of AEs will be calculated. The percentage of participants with AEs in each group will be calculated and compared using the chi-squared or Fisher’s exact test. Statistical analyses will be performed using IBM SPSS Windows version 19.0 (IBM Co., Armonk, NY, USA). The tests were two-sided; a *P* value < 0.05 will be considered statistically significant.

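### The rules that exclude randomised patients for violations do not keep their one-month ECWM, which conflicts with the stated intention-to-treat analysis and can bias the primary comparison

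*Protocol article*

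**What the plan says.** Four parts of the protocol article bear on this.

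- **Allowed or prohibited concomitant treatment.** "The use of medications or other therapies for hypophasis will be discouraged during this trial". Treatment for other chronic diseases "will be allowed if they do not change during the study period". The section ends: "If a violation occurs during the study period, the patient will be excluded from the study".
- **Withdrawal and dropout.** "Participation will be terminated at any stage if the individual refuses to continue, withdraws consent, or violates the inclusion or exclusion criteria". After consulting the review board, the investigator may also exclude participants to protect their safety or "if they are unwilling or unable to comply with the required study procedures".
- **Quality control.** "Dropouts and withdrawals from the study will be recorded based on the intervention and follow-up periods".
- **Statistical analysis.** "professionals will analyze the data using intention-to-treat and per-protocol approaches". The groups are compared by one-way ANOVA, or by Kruskal–Wallis if the data are not normal.

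Under Primary outcome, ECWM is measured at baseline, weekly during treatment, and one month after the first session.

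**The concern.** An intention-to-treat comparison needs the outcome of each randomised patient whatever happens after allocation. The two exclusion rules act after allocation, and they remove the very patients who would make the intention-to-treat result differ from the per-protocol one. If assessment stops when the patient is excluded, the two analyses converge, and the reader loses the protection that randomisation was meant to give.

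The loss need not be random. A patient who turns to another therapy for hypophasis is plausibly one whose eyelid is not improving. The rate may also differ by arm, since Group C has basic therapy only, with no extra needle. Removing poor responders flatters the arm that they leave. Losses from Group C would work against Bi'nao, and losses from Group A would work in its favour.

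This is a rule of conduct, so it cannot be repaired at the analysis stage. A later analysis plan can define sets and missing-data methods, but it cannot recover a measurement that was never taken.

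**Working it through.** **1. The plan's own figure.** The inputs under Sample size calculation are a "two-sided superiority test, where α = 0.05, power = 90"%, SD of change 1 (control) and 3 (treatment), difference 2, and 20% dropout.

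n = (1.96 + 1.28)² × (1² + 3²) / 2² = 10.4976 × 10 / 4 = 26.24, so 27 per group. Then 27 × 1.2 = 32.4, so 33 per group and 99 in total, as stated. (27 / 0.8 = 33.75 would give 34, which does not matter here.) With SD √5, since (1 + 9)/2 = 5, nominal power is 95.3% with 33 analysed per group and 89.7% with 26. Losing some patients therefore costs little power. The issue is bias.

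**2. Is the one-month ECWM of an excluded patient provided for?**

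- Study setting covers patients who stop early because they have recovered: their last ECWM and ESA count as the end-time values. It has no matching provision for violators.
- Follow-up covers all participants at three months, by clinic visit or telephone survey on progress and recurrence. That is not the one-month ECWM.
- Quality control says only that dropouts and withdrawals are recorded.
- One-way ANOVA and Kruskal–Wallis use one value per patient. A patient without the one-month value drops out unless it is imputed.

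So patients who stop early after doing well keep an endpoint, while patients excluded for a violation have none assured.

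**3. Upper bound for one arm.** This assumes normally distributed changes and that exactly the worst fraction q is removed. The mean of the remainder rises by SD × φ(z_q) / (1 − q).

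| q | Shift in SD | At SD 1 | At SD 3 |
|---|---|---|---|
| 0.10 | 0.195 | 0.20 mm | 0.59 mm |
| 0.15 | 0.274 | 0.27 mm | 0.82 mm |

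Against the target of 2, this is 10–14% at SD 1 and 29–41% at SD 3. One point is read as 1 mm, because the sample-size section speaks of points and ECWM is in millimetres. The fractions 10% and 15% are assumptions, since the document gives no violation rate.

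**4. Between-arm bias.** If a fraction f of an arm is excluded, and retained patients do better than excluded ones by D on average, the retained mean exceeds the full mean by f × D. With the same D in both arms, the bias is (f₁ − f₂) × D. For 20% versus 5% and D of 1 to 2 points it is 0.15 × 1 = 0.15 to 0.15 × 2 = 0.30. For 20% versus 0% it is 0.20 to 0.40.

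A simulation used a true difference of 0, 33 per arm, common SD √5, a two-arm t-test and 6,000 runs. The correlation is between poor outcome and exclusion, and excluded counts were rounded to whole patients.

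| Excluded, arm 1 vs arm 2 | Correlation | Spurious difference | Type I error |
|---|---|---|---|
| 20% vs 5% | 0.5 | 0.24 | 7.7% |
| 20% vs 5% | 0.8 | 0.42 | 14.0% |
| 20% vs 0% | 0.5 | 0.40 | 10.5% |
| 20% vs 0% | 0.8 | 0.65 | 21.4% |
| 20% vs 20% | 0.5 | about 0 | 6.4% |
| 20% vs 0% | 0 | about 0 | 4.9% |

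These rates and correlations are assumptions for illustration, not figures from the document.

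**The case against.** Being excluded from a study is not literally being excluded from its analysis. Because the article names both approaches, a natural reading is that violators leave the per-protocol set and stay in the intention-to-treat set. Study setting schedules ECWM for all participants, weekly values taken before exclusion would exist, and definitions of analysis sets may stand in a fuller document that is not shown.

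Part of this stands. A reader might infer that intention-to-treat cannot be done at all. The text does not support that: the patients could be kept in the set with missing or imputed outcomes, and no sentence says that assessment stops. But no sentence says that it continues either, and a patient put out of the study would ordinarily not be called back for measurement.

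A reader might also infer that Group C patients know they lack the extra needle, so that exclusion probably differs by arm. The document does not say what they know. Under Randomization and blinding, participants are blinded to the type of acupuncture. Unequal exclusion is a possibility, not a documented fact.

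Nor are all routes alike. A change in chronic-disease medication has no evident link to eyelid response, and removal for an ineligibility that predates randomisation need not depend on outcome.

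Finally, the 29–41% figure should not be read as the expected bias. It needs a perfect link between exclusion and outcome, and losses in the arm with SD 3, which is the treatment group. Losses in the control group, at SD 1, give 10–14%.

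**Conclusion.** The conflict stands on the text. Two sections remove randomised patients for events after allocation without separating treatment from assessment, and no section secures their one-month ECWM. The analysis section promises an intention-to-treat comparison that these patients would enter, at best, with the primary outcome missing.

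The primary comparison can be biased in either direction. The size cannot be derived from the document. For 10–15% removed from one arm, the upper bound is 0.20–0.27 SD of that arm. Any net bias depends on how far exclusion follows outcome and differs between arms, and it is about zero if exclusion is unrelated to outcome.

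The concomitant-treatment section is also unclear in itself. Other hypophasis therapy is only discouraged, yet a violation leads to exclusion, so what counts as a violation may be judged inconsistently.

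**What to change.** Reconcile the sections on concomitant treatment and on withdrawal with the statistical analysis section. State that:

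- violations are recorded;
- the participant continues the scheduled ECWM and ESA assessments unless consent is withdrawn;
- the participant is analysed in the randomised group in the intention-to-treat analysis;
- the violation excludes only from the per-protocol set.

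In the withdrawal section, distinguish stopping study treatment from stopping assessments. In the concomitant-treatment section, make clear which events count as a violation. Decisions on stopping treatment stay as they are.

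The change uses visits already scheduled and leaves the sample at 99. It needs an amended protocol and resubmission to the review board, as the Monitoring section requires. Recruitment was still under way according to Trial status, so the change would protect outcomes not yet collected. The statistical price is that the intention-to-treat estimate includes any effect of the other therapy. The per-protocol analysis remains beside it.

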### Outcome measures

#### Primary outcome

ECWM will be performed using a graduated ruler to measure the width (mm) between the upper and lower eyelids when the patients attempt to close his eyes. The measurements will be taken three times and the average recorded. ECWM will be performed before acupuncture therapy as the primary time measurement, weekly during the treatment duration, and at the first month after the first therapy by three physicians, and the average value recorded. The mean value and standard deviation among the participants in every group will be calculated; the differential values of eye crack width (mm) between the intervention and control groups will be compared.

#### Secondary outcome

ESA [23] will be conducted based on the muscle strength when the eyes are closed. The evaluator places the index finger on the patient’s upper eyelids and the patient will be required to close his eye. The difference in the muscle strength between the two eyelids will be recorded according to the following standard: level 5, normal contraction in affected side, which is symmetrical with the healthy side; level 4, approximately normal contraction and slightly asymmetric with healthy side; level 3, strength is approximately half of the healthy side; level 2, strength is approximately one-quarter of the healthy side; level 1, a slight muscular contraction in the affected side; level 0, no sign of muscle contraction in the affected side. Assessment will be performed at the time points mentioned above and at the first month after the therapy by three physicians, and the average value will be recorded. Levels 0–5 will be endowed with numeric values 0–5 as the ESA score; the average score among the participants in each group will be calculated. The mean value and standard deviation of ESA scores between the intervention and control groups will be compared.

#### Follow-up

All participants will be followed up at three months after the first acupuncture therapy, including those who completely recovered from hypophasis within one month. The follow-up will be accomplished by a clinic visit or telephone survey about the progress and recurrence of hypophasis.

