## Background

Bell’s palsy is a type of self-limited peripheral neuropathy with uncertain pathogens. Patients with Bell’s palsy suffer from dysfunction of the facial nerve and inflexible muscle movements; the majority of them will recover within 1–3 months. However, a few of them will undergo a long recovery procedure and/or leave some sequelae such as deviation of mouth angle, hemifacial spasm, or hypophasis [1, 2].

Hypophasis is frequently observed among some patients with Bell’s palsy, who are almost at complete recovery, and is occasionally accompanied with a tiny droopy corner of the mouth, which is the major obstacle before full recovery from Bell’s palsy, as well as posing huge difficulties for doctors or rehabilitation physicians. The syndrome of hypophasis will continue to maintain the status quo unless appropriate therapy is applied; however, over-treatment such as excessive exercise or transcutaneous electrical nerve stimulation may lead to facial spasm [3, 4].

Acupuncture therapy has been widely used for the treatment of Bell’s palsy in China and worldwide [5–8]. Although the efficacy of the therapy has not been sufficiently proved by systematic reviews [9], its application has been considered a reasonable resolution for the management of some symptoms such as hypophasis. Although acu-points around the eye socket are frequently selected in the approach of acupuncture therapy, high-efficiency widely accepted acu-points have not yet been reported.

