### Safety issues

Adverse events (AEs) will be recorded using the standard operating procedures for monitoring and reporting all AEs, which refer to all the harmful and unintended reactions that occur during the acupuncture treatment. The symptoms, date of occurrence, disappearance, causality, and severity of the AEs will be recorded. The putative AEs of acupuncture include the following: local bleeding or hematoma; more than slight sharp pain; aggravation of symptoms; syncope; nausea; headache; peripheral nerve injury; and infection. Participants will be informed of the potential AEs in advance.

During the study period, all researchers will ensure patient safety. When SAEs occur, the researchers will immediately halt the study and promptly provide appropriate management. The PI will also report the AEs to the IRB and halt the study partially or completely until further notice. Then, the IRB will determine whether the clinical study can be continued. The trial will be stopped if the IRB speculates unacceptable risks of SAEs. The hospital provides insurance coverage for harm associated with the interventions during this trial as necessary.

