### Ethics and dissemination

The study was planned in accordance with the Helsinki Declaration and the Korean Good Clinical Practice Guidelines to protect the participants and was approved by the Medical Ethics Committee Board of Baoshan Hospital of Integrated Traditional Chinese Medicine and Western Medicine, Shanghai (201709–02). The participants will be informed of the potential benefits, risks, alternatives, and responsibilities of the study by the researchers during the consent process. They will be fully aware that they are free to withdraw from the study at any time. Any AEs (described as unfavorable or unintended signs, symptoms, or diseases occurring after treatment) related to acupuncture treatment will be observed and reported by patients and practitioners during each patient visit. In addition, all vital signs and AEs will be measured and recorded during each visit. The findings will be disseminated in peer-reviewed journals and conference presentations.

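### Facial spasm is named in the Background as a harm and a sequela but is not a solicited adverse event, and after month 1 its capture depends on a spontaneous report and on which of two AE definitions applies

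*Protocol article*

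**What the plan says.** All references are to the protocol article.

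- **Background.** Spasm appears twice. Slow recovery may "leave some sequelae such as deviation of mouth angle, hemifacial spasm, or hypophasis", and "over-treatment such as excessive exercise or transcutaneous electrical nerve stimulation may lead to facial spasm".
- **Safety issues, list.** "The putative AEs of acupuncture include the following: local bleeding or hematoma; more than slight sharp pain; aggravation of symptoms; syncope; nausea; headache". The list ends with peripheral nerve injury and infection. Facial spasm is not on it.
- **Safety issues, definition.** AEs are "all the harmful and unintended reactions that occur during the acupuncture treatment".
- **Ethics and dissemination.** AEs are "described as unfavorable or unintended signs, symptoms, or diseases occurring after treatment", and "all vital signs and AEs will be measured and recorded during each visit".
- **Follow-up.** There is one contact, three months after the first session. "The follow-up will be accomplished by a clinic visit or telephone survey about the progress and recurrence of hypophasis".
- **Table 1 and Study setting.** Treatment is 12 sessions over 4 weeks and stops earlier on complete recovery.
- **Primary and Secondary outcome.** The last scheduled lid-gap measurement (ECWM) and eyelid-strength score (ESA) are at month 1. ECWM is the gap in mm on attempted closure. ESA runs up to normal, symmetrical contraction and has no level above that.
- **Statistical analysis.** The percentage of participants with AEs is compared between groups by a chi-squared or Fisher's exact test.

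**The concern.** The abstract gives safety as one of the things the study assesses, and the article's Discussion already describes the treatment as safe. Spasm is the one harm that the Background links to treating this condition too vigorously, yet most of the listed AEs are general needling events. The single late contact is worded around the target symptom alone. A patient whose lid gap has not returned but who has developed spasm can truthfully report no recurrence, and nothing in the stated content of that contact prompts the other answer.

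The two AE definitions make this worse. Under the one in Safety issues, spasm that begins after the last session is not an AE. Under the one in Ethics and dissemination, it is. What is at stake is what the safety table can support: an absence of spasm in it could mean that none occurred, that nobody asked, or that the narrower definition was applied.

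**Working it through.** **1. The AE window, with the sections side by side**

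| Section | What counts as an AE | When it is recorded | Month-3 telephone contact covered? |
|---|---|---|---|
| Safety issues | Any harmful, unintended reaction, but only during treatment | Under SOPs | No |
| Ethics and dissemination | Unfavourable signs or symptoms after treatment | At each visit | Not stated |
| Follow-up | AEs not mentioned | Once, at month 3, by visit or telephone | Topic is hypophasis |

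For spasm that starts after treatment, the outcome depends on the route:
- At a clinic visit with the Ethics definition, it is recorded if the patient mentions it or the examiner sees it.
- At a clinic visit with the Safety definition, it falls outside the window.
- By telephone, no AE enquiry is stated under either definition.

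**2. Length of the gap**

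Inputs: treatment of about 1 month (Table 1) and follow-up at 3 months from the first session (Follow-up).
- 3 − 1 = 2 of 3 months lie after treatment.
- For recovery at week 2, 13 − 2 = 11 of 13 weeks lie after treatment. Study setting leaves unclear whether the weekly and one-month assessments continue for such a patient, so 11 weeks is an upper figure for time without a visit.

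This is elapsed time, not a count of missed cases.

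**3. What 33 per arm could show**

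The plan's own figure first: n = (1.96 + 1.28)² × (1² + 3²) / 2² = 10.4976 × 10 / 4 = 26.24, and 26.24 / 0.8 = 32.8, so 33 per arm. This reproduces, and nothing here changes it.

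The protocol gives no spasm rate, so the rates below are assumptions. The chance of at least one case in an arm, if everyone is asked, is 1 − (1 − p)^33:

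| Assumed rate p | Chance of at least one case among 33 |
|---|---|
| 1% | 28% |
| 2% | 49% |
| 5% | 82% |
| 10% | 97% |

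Power to separate 5% from 15% between two arms (normal approximation, two-sided 0.05):
- SE under the null = √(2 × 0.10 × 0.90 / 33) = 0.0739.
- SE under the alternative = √((0.05 × 0.95 + 0.15 × 0.85) / 33) = 0.0728.
- z = (0.10 − 1.96 × 0.0739) / 0.0728 = −0.61, so power is about 27%.

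Asking would probably reveal whether spasm occurs at all if it is not rare. It would not support a comparison between arms.

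**4. Could spasm by month 1 affect ECWM?**

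Assume that a share q of an arm has a gap narrowed by w mm through spasm. The arm mean then moves by q × w.
- q = 5%, w = 1 to 3 mm: 0.05 to 0.15 mm.
- q = 10%, w = 1 to 3 mm: 0.1 to 0.3 mm.

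The planned difference is 2. At these rates the effect is small, and its direction is itself an assumption.

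**The case against.** The strongest reply is that the plan already covers spasm. The AE list is open, it includes aggravation of symptoms and peripheral nerve injury, and the definition above it takes in every harmful, unintended reaction. Ethics and dissemination extends this to signs after treatment and records AEs at each visit. Safety issues also refers to standard operating procedures, and the detail of form items and telephone scripts is commonly left to such documents. Much of this stands. A reader might infer that late spasm must go unrecorded, and the documents do not support that, because a report at a month-3 clinic visit can be captured.

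Two further readings are tempting and also fail:

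- **That the extra needle would make spasm more frequent.** The Background's examples of over-treatment are exercise and electrical stimulation, not acupuncture. Bi'nao is in the arm, the facial needling is the same in all three groups, and Groups A and B both receive one extra arm needle.
- **That late spasm would be scored as benefit.** Neither ECWM nor ESA is scheduled after month 1, and no three-month success outcome is defined.

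What the reply does not remove is text that the article itself states: two AE definitions with different windows, and a late contact whose stated subject is hypophasis alone and which may be a telephone call.

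**Conclusion.** The point holds in a limited form. Spasm, which the Background names as a harm and a sequela, is not a listed AE. After month 1, its capture rests on a spontaneous report and on which AE definition is applied, and no AE enquiry is stated for the telephone route. This affects about two of the three months of observation. No number of missed cases can be given, because the documents contain no spasm rate.

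The efficacy analysis is not threatened. At most, spasm already present by month 1 might narrow ECWM, by 0.05 to 0.3 mm in an arm's mean under the assumed rates and narrowing above. The consequence lies on the safety side: as written, a table without spasm would be weak evidence that none occurred. The correction is inexpensive and worth making.

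**What to change.** 1. Reconcile the AE definitions in Safety issues and in Ethics and dissemination, so that one window runs through month 3 and applies to both clinic and telephone contacts.
2. Name facial spasm of the affected side in Safety issues as a solicited event. Record it with one fixed yes/no item and an onset date at each weekly assessment, at one month, and in the three-month visit or telephone script under Follow-up.
3. In Statistical analysis, tabulate spasm by arm descriptively, and state that 33 per arm gives little power for a comparison.

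The cost is one case report form line and one script question at contacts already planned. Sample size and visit schedule stay as they are. The downside is a few more recorded AEs and a slightly less favourable safety table.
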